## Abstract

**Background:**

Social media has become a central channel for the dissemination of health information, enabling rapid sharing of evidence-based guidance while also facilitating the spread of inaccurate or misleading content. Exposure to such information has been associated with changes in vaccination-related attitudes and decision-making. These effects may not occur uniformly across populations, and there is limited understanding of how health information circulates within Spanish-language social media networks or which communication strategies are most effective in promoting engagement and informed decision-making. This study describes a protocol to evaluate a community-engaged intervention designed to address these gaps.

**Methods:**

This study will use a non-randomized stepped-wedge design to evaluate the implementation and effectiveness of the Dime La VerDAD intervention across community-based cohorts of promotores de salud in Chicago. Promotores will be grouped into geographically defined clusters and will transition from control to intervention at six-month intervals, such that all clusters receive the intervention by study end. The intervention will consist of a structured, bilingual training program focused on identifying inaccurate health claims, evaluating source credibility, and developing accessible, evidence-based social media content, including narrative-based messaging. Outcomes will be assessed using surveys, focus groups, social media analytics, and publicly available epidemiologic data. Primary and secondary outcomes will include changes in knowledge, communication practices, engagement with social media content, and vaccination-related decision-making. Analyses will use mixed-effects models to evaluate changes over time while accounting for clustering and repeated measures.

**Discussion:**

This study will generate evidence on how health information is shared and interpreted within Spanish-language social media networks and evaluate whether a structured, community-engaged communication intervention improves the quality and reach of health messaging. Findings will inform the development of scalable, community-based strategies to support dissemination of reliable health information and promote informed decision-making in diverse populations.

**Trial registration::**

ClinicalTrials.gov
NCT06417762. Recruitment has begun and is ongoing at the time of manuscript submission.

## Background

Social media has become a primary channel for the dissemination of health information, enabling the rapid sharing of evidence-based medical guidance across broad audiences. At the same time, these platforms also facilitate the widespread circulation of inaccurate or misleading health information, shaping how individuals access, interpret, and act on health content [1]. During the COVID-19 pandemic, vaccine-related discussions expanded substantially across social media, accelerating both the volume and visibility of health-related messages and contributing to uncertainty about recommended immunizations [2]. As social media continues to play a central role in health communication, understanding how health messages are conveyed and received in these environments is critical for public health.

Exposure to inaccurate or misleading health information on social media has been associated with measurable changes in vaccination-related attitudes and decision-making [3, 4]. Such exposure can shape how individuals interpret risk, assess the credibility of scientific evidence, and determine whether to pursue recommended immunizations. During the COVID-19 pandemic, for example, widespread circulation of conflicting health claims on social media was associated with changes in perceptions of vaccine safety and reduced adherence to public health guidance, particularly in the context of uncertainty and rapidly evolving evidence [5–8]. Social media has similarly emerged as a key source of vaccine-related information for seasonal influenza, where variation in message content and source credibility has been associated with differences in vaccination behavior and uptake [6–9]. These patterns thus underscore the importance of understanding how health information is encountered and interpreted within social media environments.

However, the effects of health information on social media may not occur uniformly across populations. Differences in social networks, access to information, and trusted sources can shape how health information is accessed, interpreted, and shared across communities [10–12]. These considerations are particularly relevant for Spanish-speaking communities, where the pathways through which health information circulates, the sources perceived as credible, and the reception of health information have not been well characterized [13–15]. For example, studies have shown that Spanish-speaking individuals may face challenges accessing trusted health information and often rely more heavily on social media and interpersonal networks for health-related content [16]. Levels of trust in health information sources also vary substantially within Spanish-speaking communities, further shaping how health messages are received and acted upon [17]. Understanding these differences is essential for interpreting how health information circulates within and across social media networks [18, 19].

In this context, understanding which characteristics of health messages influence how information is interpreted and shared on social media is also critical. Prior research suggests that message format plays an important role in shaping engagement and comprehension, with health messages that incorporate personal narratives often perceived as more relatable and easier to understand [20]. In addition to message characteristics, the credibility of the information source influences how messages are received and acted upon. Information delivered by trusted community communicators can shape attitudes and information-sharing behaviors, particularly when messages are conveyed by individuals with established relationships within their communities [21]. For example, collaborative efforts between healthcare professionals and community-based communicators have demonstrated the feasibility of producing culturally and linguistically appropriate health content for Spanish-speaking communities [22–24]. Similarly, in Illinois, promotores de salud (community health workers) have played an important role in disseminating health information within Spanish-speaking communities, including during the COVID-19 pandemic.[25][21] These findings highlight the importance of both message characteristics and source credibility in shaping how health information is understood and shared.

Despite this work, there remains a limited understanding of how health information circulates and is interpreted within Spanish-language social media networks. In particular, few studies have examined how inaccurate or misleading health information is encountered in these settings or how responses grounded in scientific evidence are received by community members. In addition, it remains unclear which communication approaches are most effective in promoting engagement, recall, and informed decision-making in real-world social media environments. Addressing these gaps is essential for developing effective and scalable approaches to communicating evidence-based health information within Spanish-speaking communities.

To address these gaps, we developed Dime La VerDAD (“Tell Me the Truth”: Verify, Debunk, and Disseminate), a structured, community-engaged social media training program designed to support promotores de salud in disseminating reliable, evidence-based information about respiratory virus prevention. The program is grounded in principles of health communication and is designed to build practical skills in identifying inaccurate health claims, developing clear and accessible messages, and engaging effectively with social media audiences.

This study will evaluate the implementation and effectiveness of the Dime La VerDAD program using a stepped-wedge design across community-based cohorts. Specifically, it will characterize how health information is shared and interpreted within Spanish-language social media networks, evaluate whether a structured, evidence-based communication training program improves the quality and reach of health messaging, and assess whether narrative-based approaches differ from standard informational content in influencing engagement and vaccination-related decision-making. We hypothesize that promotores will be perceived as trusted messengers and that narrative-based posts will result in greater engagement and improved decision-making in favor of recommended immunizations.

## Methods

### Study Design

This study will use a non-randomized, stepped-wedge design to evaluate the implementation and effectiveness of the Dime La VerDAD intervention across community-based cohorts of promotores de salud. Promotores will be enrolled in clusters defined by the geographic areas in which they provide services. Three clusters will include promotores serving two geographically adjacent communities, and one cluster will include promotores serving a single, geographically distinct area. Each cluster will include approximately 5–14 promotores, depending on the number of communities represented, with larger clusters corresponding to areas serving multiple adjacent neighborhoods. This cluster structure was informed by pilot data indicating that promotores frequently serve multiple neighboring communities; grouping adjacent areas is intended to reduce contamination across study conditions and minimize spillover effects.

At six-month intervals, each cluster will transition from the control condition to the intervention, such that all clusters will receive the intervention by the end of the study period. During the control phase, promotores will continue their usual social media practices without structured training or guidance from the study team. Upon transition to the intervention phase, participants will complete a structured science communication curriculum and apply these principles by developing and sharing social media content within their networks.

Outcomes will be compared within clusters over time, with each cluster serving as its own control, and between clusters as sequential crossover to the intervention occurs. This design allows for both within-cluster and between-cluster comparisons while accounting for secular trends in social media use and vaccination-related attitudes.

### Study Setting

This study will be conducted in community settings across selected neighborhoods in Chicago characterized by lower immunization coverage and higher rates of respiratory virus infection [26]. Zip codes and community areas of interest are shown in Fig. 1 and include Gage Park, Chicago Lawn, Hermosa, Belmont Cragin, Humboldt Park, Brighton Park, and Eastside, which were designated under the Protect Chicago Plus program in response to the COVID-19 pandemic [27].

Study activities will take place in person at promotores’ worksites or community locations, as well as virtually via Zoom using bilingual (English and Spanish) instructors.

### Participants

We will recruit promotores de salud from community-based organizations serving the designated study areas. Eligible participants will include promotores who are 18 years of age or older, fluent in English or Spanish, provide services in at least one of the designated community areas, and maintain a personal or work-related social media presence. Promotores will be excluded if they plan to discontinue their work prior to completion of data collection, are unable to communicate in English or Spanish, do not serve the designated community areas, or decline participation in study-related social media activities.

Promotores will be recruited through established partnerships with community-based organizations. Recruitment strategies will include distribution of study materials through organizational networks, presentations at community meetings, and referral through organizational leaders. Promotores may also self-nominate or be referred by community-based partners. Only individuals who directly express interest or provide contact information for follow-up will receive recruitment communications from the study team. Interested individuals will be screened by telephone to confirm eligibility and enrolled into cohort groups based on the communities they serve. Purposive sampling will be used to prioritize bilingual (English/Spanish) or Spanish-speaking promotores serving the designated community areas.

Participation in the study will be voluntary for all participants. Promotores will be provided with an information sheet describing study procedures, potential risks and benefits, confidentiality protections, and data-sharing plans prior to participation in any study activities. Members of the research team will review this information with participants and provide opportunities to ask questions. Consent will be indicated through voluntary participation in study activities, including surveys, focus groups, and social media engagement. Participants may decline specific activities or withdraw from the study at any time without penalty.

Members of promotores’ social media networks will be recruited through posts shared within existing social media platforms. Interested individuals will be directed to a survey link or QR code, where they will receive an electronic information sheet describing the study purpose, voluntary nature of participation, data to be collected, and confidentiality protections. Completion of the survey will indicate implied consent. No consent language will be posted publicly on social media platforms.

Promotores who discontinue participation will be invited to participate in an optional feedback session to identify barriers to engagement. These sessions will be facilitated by study staff not involved in curriculum delivery to encourage open discussion.

Promotores will be compensated at a rate of $30 per hour for structured activities, including surveys, focus groups, and training sessions. During the campaign period, participants will also receive $30 per month for ongoing activities, including social media posting and sharing engagement data. Members of promotores’ social media networks will receive $10 gift cards for each completed survey (baseline, mid-campaign, and post-campaign), with an additional incentive provided for completion of the final follow-up survey.

### Intervention

The Dime La VerDAD intervention will be a structured, community-engaged social media training program designed to support promotores de salud in disseminating reliable, evidence-based information about respiratory virus prevention within their social media networks. The program will be grounded in principles of health communication and will focus on building practical skills in identifying inaccurate health claims, evaluating information sources, and developing clear and accessible health messages.

The curriculum will include training in infographic design, assessment of source credibility, and strategies for communicating effectively across diverse audiences. Participants will be guided in incorporating personal narratives into their social media posts and in responding constructively to disagreement in online environments. As part of the program, promotores will also develop original social media content, including infographics and accompanying captions, and will share these posts within their existing social media networks. Content will be iteratively refined through structured feedback from instructors and peers. A detailed outline of session topics, activities, and assignments is provided in Table 1.

The intervention will be delivered through a series of structured training sessions led by bilingual instructors. Sessions will be conducted in a hybrid format, with options for in-person or virtual participation, and will be supplemented by independent work focused on content development and social media engagement. Across the program, each cohort will complete approximately 18 hours of structured training.

To support adherence and minimize attrition, the study will implement a multi-pronged retention strategy that accounts for potential barriers such as scheduling constraints, competing work responsibilities, and other personal obligations. This approach will include flexible scheduling to accommodate participants’ availability, regular reminder communications regarding study activities, and financial compensation for participation.

### Outcomes

Outcomes will be assessed using a combination of surveys, focus groups, social media analytics, and publicly available epidemiologic data to characterize social media practices, evaluate engagement with the training program, and assess the effectiveness of communication strategies.

### Surveys

Surveys will be administered to promotores and members of their social media networks at multiple time points aligned with the stepped-wedge rollout.

At baseline, promotores will complete a 30-minute survey assessing demographics, social media use patterns, and confidence in applying science communication principles related to respiratory virus prevention [28]. The survey will capture social media platform use, including applications used, number of network members, and frequency of reading, posting, and sharing content, as well as experience addressing vaccine-related health claims. These data will be used to describe variability in social media practices, identify emerging platforms for inclusion in analyses, and characterize posting behaviors across community areas. Survey items will draw from the PhenX Toolkit [29], including modules on social determinants of health, COVID-19 exposure, technology access, and media use.

Promotores will also complete brief surveys immediately before and after the training to assess learning related to evaluating online health information, assessing source credibility, and developing evidence-based messages. Post-training surveys will also capture perceived usefulness, acceptability, and feasibility of the training. Implementation outputs will be documented by tracking completion of curriculum assignments and the number and characteristics of infographics and posts produced (e.g., inclusion of credible sources, use of narrative elements).

Additional follow-up surveys will be administered at study conclusion to assess perceived reach, communication experiences, and confidence in applying science communication strategies.

Members of promotores’ social media networks will complete surveys at baseline, at 6-months, and post-campaign to assess exposure to social media content, recall, perceived credibility, and vaccination-related decision-making.

Individuals who wish to receive compensation for completing the surveys will be asked to provide their email address. This contact information will not be stored with survey response data.

Survey data will be collected and managed using REDCap (Research Electronic Data Capture) electronic data capture tools hosted at the University of Iowa [30, 31]. REDCap is a secure, web-based software platform designed to support data capture for research studies, providing 1) an intuitive interface for validated data capture; 2) audit trails for tracking data manipulation and export procedures; 3) automated export procedures for seamless data downloads to common statistical packages; and 4) procedures for data integration and interoperability with external sources.

### Focus Groups

Qualitative data will be collected through focus groups or individual interviews with promotores, depending on participant preference, conducted at baseline and following completion of the intervention. Baseline focus groups and interviews will be 60–90 minutes in duration and will be guided by an interview protocol informed by the Appreciative Inquiry framework, an asset-based approach designed to elicit strengths, opportunities, and communication strategies within local contexts.[32] Discussions will assess health information sources, commonly encountered vaccine-related claims, trust in information sources, perceptions of vaccine safety, and vaccination-related decision-making.

Post-intervention focus groups and interviews will explore experiences with the training program, community responses to social media content, engagement patterns, and examples of successful message dissemination or constructive disagreement.

We expect to have 5 to 10 participants per focus group session. Focus groups will be conducted in English and Spanish and will take place in person or virtually (via Zoom), based on participant preference.

### Social Media Engagement

Social media data will be collected from platforms commonly used within participants’ networks, including Facebook and Instagram. Promotores will be trained to export data from their posts (e.g., Facebook JSON exports) and share these files with the research team. For platforms that do not support direct data export, alternative approaches will be used, including participant-reported metrics or researcher access to social media groups or communication channels, as appropriate.

Engagement metrics will include impressions (i.e., number of users who view a post) and indicators of interaction such as likes, comments, and shares. In addition, the content of promotores’ posts and associated audience responses will be analyzed to characterize features of communication, including sentiment, use of personal narratives, and incorporation of scientific evidence. These measures will be used to examine how characteristics of social media content relate to engagement within promotores’ networks.

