### Social Media Engagement

Social media engagement will be quantified using platform-derived metrics, including impressions, likes, comments, and shares. Count-based outcomes will be analyzed using Poisson or negative binomial regression models, as appropriate based on dispersion characteristics. Continuous or ordinal survey outcomes will be analyzed using linear or cumulative link mixed models, depending on distributional assumptions. Repeated measures of generalized linear mixed models will be used to assess changes in engagement over time while accounting for clustering within promotores and neighborhood clusters under the stepped-wedge design.

Characteristics of social media posts and audience responses will be extracted using large-language models and multimodal analytic approaches applied to text, images, and video content. These characteristics will include sentiment, discussion of personal experience, presence of scientific evidence, and patterns of agreement or disagreement. These features will be incorporated as independent variables in regression and machine learning–based predictive models to examine their association with engagement outcomes and to identify characteristics of posts associated with higher levels of interaction within promotores’ social networks.

In addition to quantifying the volume of engagement, analyses will examine the nature of engagement by evaluating the content of audience responses to promotores’ posts. These analyses will provide insight into how different types of communication strategies influence both the extent and quality of interaction.

Implementation fidelity will be assessed by quantifying the number and characteristics of posts produced, including adherence to training principles such as inclusion of credible sources and use of narrative elements.

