## Figures and Tables

**Figure 1 F1:**
[figure not shown]
Geographically distinct community areas used for the recruitment of promotores.

**Table 1 T1:** Dime La VerDAD curriculum structure.

Session	Topic	Details	Homework
Focus Group	Baseline Discussion	Structured discussion to understand current social media practices, commonly encountered health claims, and communication experiences	
1	Designing Infographics	Introduction to infographics and visual communication principles; overview of Canva tools	• Join the study communication group (on WhatsApp) • Friend/follow *Dime La VerDAD* on social media platforms • Access the Canva folder • Share 2–3 practice posts on social media
2	Understanding Inaccurate Health Claims	Overview of different types of inaccurate health information and how it circulates online; discussion of potential impacts	• Invite approximately 45 social media network members to complete the pre-survey • Identify one vaccine-related health claim to address ○ Locate 2–3 credible sources • Begin drafting an infographic in Canva
3	Communicating Across Audiences	Principles of effective communication and audience engagement	• Develop draft infographics (1 Facebook, 1 Instagram) ○ Include a link to a credible resource • Draft a caption incorporating a personal narrative ○ Include (2–3) relevant hashtags and tags as appropriate
4	Evaluating Source Credibility	Methods for assessing the reliability of online sources (e.g., SIFT method, fact-checking tools)	• Verify sources using structured evaluation methods ○ Identify additional credible resources if needed • Revise draft infographic and caption based on instructor and cohort participant feedback
5	Applying Science Communication Strategies	Strategies for making evidence-based messages engaging and understandable	• Refine your infographic and caption based on feedback • Post standardized informational content provided by the study team
6	Responding to Disagreement on Social Media	Approaches to addressing dissent constructively and maintaining professionalism online	• Develop a strategy to address responses from people with opposing views • Present final infographic and communication strategy • Post standardized informational content provided by the study team • Post your finalized infographic and caption • Six months after baseline focus group, invite social media network members to complete the post-survey

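### Impressions are classed as engagement and the count models name no exposure term, so the narrative-versus-standard engagement comparison mixes reach with viewer response

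*Protocol article*

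**What the plan says.** The protocol article deals with engagement in two places. Under Methods, Social Media Engagement: "Engagement metrics will include impressions (i.e., number of users who view a post) and indicators of interaction such as likes, comments, and shares". Under Data Analysis, Social Media Engagement: "Social media engagement will be quantified using platform-derived metrics, including impressions, likes, comments, and shares". That second section continues: "Count-based outcomes will be analyzed using Poisson or negative binomial regression models, as appropriate based on dispersion characteristics". It adds that mixed models will "assess changes in engagement over time while accounting for clustering within promotores and neighborhood clusters under the stepped-wedge design". Neither section mentions an offset, a rate, or interactions per view or per follower.

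Engagement carries a stated hypothesis. The Background expects that "narrative-based posts will result in greater engagement and improved decision-making in favor of recommended immunizations", with standard informational content as the comparator. The same paragraph makes the reach of messaging an aim of its own, but impressions are listed only under engagement and no metric is set aside for reach.

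Table 1 describes the two kinds of post. In Session 3 the promotor drafts a caption containing a personal narrative and is told: "Include (2–3) relevant hashtags and tags as appropriate". In Sessions 5 and 6 the promotor also shares ready-made posts supplied by the study team. No hashtag or tag instruction is given for those.

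**The concern.** A like, comment or share is a reaction from someone who saw the post. An impression only records that someone saw it. With both classed as engagement, a post shown to more people counts as more engaging on impressions by definition. It will also tend to collect more likes, comments and shares even if each viewer is no more responsive.

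The narrative hypothesis is where this matters. It is about whether a personal story moves viewers more than standard content does. If the narrative posts also carry hashtags and tags, which can plausibly change who sees a post, a difference in raw counts could come from the story, from the visibility tools, or from both. The same holds for the models relating post features to engagement: the features listed there cover sentiment, personal experience, scientific evidence and agreement or disagreement, and do not mention views, platform or hashtags.

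**Working it through.** The protocol states no rate, effect size or power for engagement, so there is no figure of its own to reproduce. The check has three parts.

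**1. The identity.** For one type of post, let V be the mean number of viewers, r the interactions per viewer, and C = V × r the mean interaction count. For narrative (1) against standard (0) posts:

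C1/C0 = (V1/V0) × (r1/r0)

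A count model without an exposure term estimates the left side. The question about viewer response concerns r1/r0. Impressions analysed as an outcome estimate V1/V0 alone and carry no information on response.

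**2. Illustrations (all inputs assumed).**
- Constant response of 5%, views up from 100 to 150: 0.05 × 100 = 5 and 0.05 × 150 = 7.5, so the count ratio is 7.5/5 = 1.5. The per-view ratio is 0.05/0.05 = 1.0.
- Reach doubled, per-view response down 40%: 2 × 0.6 = 1.2. Raw counts show a 20% gain where viewer response fell.
- Reach halved, per-view response doubled: 0.5 × 2 = 1.0. Raw counts show nothing where viewer response rose. The distortion can go either way.

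**3. Does promotor-level clustering remove it?** This was simulated with 200 runs per scenario. Only the 35 promotores come from the protocol (its stated minimum). The rest is assumed: two groups of 10 posts per promotor, a median of 200 impressions, a 5% interaction rate, and variation in reach between promotores and between posts. The model was Poisson with promotor intercepts (fixed effects standing in for random ones) and dispersion scaling. The two groups were generated as control and intervention phases. The structure is the same for two kinds of post from one promotor.

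| Reach ratio | True per-view ratio | Count ratio, no offset | Ratio with log(impressions) offset |
|---|---|---|---|
| 1.0 | 1.0 | 1.00 | 1.00 |
| 1.25 | 1.0 | 1.25 | 1.00 |
| 1.5 | 1.0 | 1.50 | 1.00 |
| 2.0 | 1.0 | 2.00 | 1.00 |
| 3.0 | 1.0 | 3.01 | 1.00 |
| 2.0 | 0.6 | 1.20 | 0.60 |

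In every scenario with a change in reach, the model without the offset was significant in all 200 runs. Promotor intercepts absorb stable differences in audience size between promotores. They leave untouched a difference in reach between one promotor's own posts.

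The simulation builds in the reach difference and recovers it. It shows that the adjustment does not help and that the offset does. It says nothing about how large the reach difference will be in this trial.

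**The case against.** **Silence is not exclusion.** An offset is a routine part of a Poisson or negative binomial model, and an article may leave it to an analysis plan that is not shown. This stands: a reader might infer that the plan rules out any denominator, and the text does not say so. What does not depend on an unseen document is the classing of impressions as an engagement outcome, which the article states twice.

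**The metrics are listed separately.** A reader might infer that impressions are added to likes, comments and shares in one score. No composite is stated, so that reading is unsupported.

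**Reach is a stated aim.** If training in hashtags and tags brings more viewers and more total interactions, that is part of the training effect. This stands. Raw totals are a legitimate estimand for the overall effect. They are unsuited only to the narrower question of whether the narrative makes viewers respond more.

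**Views are not a neutral denominator.** They are counted after posting, and a share puts the post before more people, so dividing by views can penalise a post that spread because people shared it. This stands, and it is why a per-view rate cannot be the only analysis.

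**Network size looks like a ready substitute where views are missing.** Under Methods, Surveys: "The survey will capture social media platform use, including applications used, number of network members". But this is a baseline figure for each promotor. It does not vary between that promotor's posts, so it cannot correct a within-promotor comparison.

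**Table 1 should not be stretched.** A reader might infer that each campaign post goes out on two platforms, or that the study account and fellow trainees inflate the counts. The table asks for one Facebook and one Instagram draft, for the promotor to follow the study account, and for the promotor to join a messaging group. It does not say that finished posts appear on both platforms or that the account or peers interact with them.

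**Conclusion.** The point holds in limited form. The article puts viewers and responses under one heading and names count models with no exposure term. For the narrative-versus-standard comparison, where Table 1 attaches hashtags and tags to one type of post and is silent on the other, raw interaction counts cannot separate wider reach from stronger response.

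The multiplicative identity needs no assumption: a k-fold difference in reach multiplies the count ratio by k. The value of k is unknown. The documents give no view or interaction rates and do not show that narrative and standardized posts differ in reach, so it would be wrong to infer that the narrative result is biased by any given amount or in a given direction.

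The primary outcome, survey-reported vaccination decision-making in the network members, and its sample size are unaffected. The feature models are described as examining association, so the issue there is which association is estimated. The change is worth making because it is cheap and bears on a named hypothesis, but it concerns a non-primary outcome.

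**What to change.** 1. Report impressions as reach, under that name. This also gives the stated reach aim a metric.
2. Keep total likes, comments and shares as the overall effect of the training.
3. For the narrative-versus-standard and post-feature analyses, add interactions per viewing user: the planned Poisson or negative binomial mixed model with log(impressions) as an offset and platform as a covariate, restricted to posts with a recorded view count.
4. Do not substitute baseline network size in these within-promotor comparisons.
5. Present reach, total interactions and the per-view rate side by side, and note that shares can raise views.

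The cost is wording and one added model per analysis. No new data are needed for posts whose view counts are already captured, and the article says data collection is not complete, so the change can be recorded before analysis. The price is that posts without a view count drop out of the per-view analysis. The article foresees platforms without direct export, so the number and type of posts excluded should be reported.
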